### Procedure

Each participant will have a total of 12 individual music therapy sessions in their home, delivered twice weekly over the course of 6 weeks. They will not be required to perform any practice or exercises set by the researcher between sessions. Whilst in wait list, before the intervention begins, participants will not receive any community nor privately employed rehabilitation interventions for upper limb hemiparesis. Each participant will also receive the Action Research Arm Test (ARAT) (Lyle, 1981) and Nine Hole Peg Test (9HPT) (Kellor et al., 1971) assessments at the same five time points after baseline measure, over an 18 week period as follows: Timepoint 1 at Week 1 after randomization; timepoint 2 at week 6; timepoint 3 at week 9; timepoint 4 at week 15; and timepoint 5 at week 18. The design will allow analysis of treatment and no treatment by comparing treatment group with wait list group data. It will also be possible to compare early versus late intervention following discharge from the community rehabilitation treatment, as the wait list participants will have a delay of 9 weeks between community discharge and beginning TIMP. Data collected from wait list group participants prior to TIMP treatment will be analyzed to determine whether there has been any spontaneous change in upper limb function, which can occur as an independent covariate (Kwakkel et al., 2006). Subject data from the ARAT and 9HPT will also be individually analyzed in order to discuss group results.

Although unusual in a randomized cross-over design study, qualitative data will be collected from each participant in order to explore patient preference with regard to using music to support exercises, and factors that might provide insights into patient tolerance and compliance. These aspects are important given the innovative treatment being used, the dosage and the setting i.e., within the home environment. Qualitative data will be collected by the researcher immediately before and after the 6 weeks of TIMP, by using a semi-structured interview that has been devised for this study and comprises five questions regarding the participant's experience of playing the instruments and playing to the music. This data will provide an overall impression of the feasibility for this treatment protocol. Participant responses to the post semi-structured interview will specifically provide data regarding motivational effects. In addition, the researcher will gather information in a research journal during and after each session, which will describe emotional responses; no direct quotes from participants will be used. There is also a five point Likert scale for recording how much participants feel the treatment will help them and, at the end of the 6 weeks of TIMP, how much they feel it actually has helped them in their ADLs. The researcher will record, in written form, participants' responses during the interview for later thematic analysis. Open questions will be used to give participants the opportunity to express their preconceptions and communicate their experience of the treatment, with the possibility of other themes arising. The quantitative data gained with the Likert response scale is used to record a time series of treatment responses (control for auto-correlation is not intended).

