Frequency of therapy sessions in existing studies has been predominantly 5 days per week for 3–4 weeks (Schneider et al., 2007; Altenmüller et al., 2009; Malcolm et al., 2009a; Rojo et al., 2011; Amengual et al., 2013), which is comparable with typical modified constraint induced movement therapy (mCIMT) delivery (Earley et al., 2010), and the music therapy treatment has usually been compared with other forms of standard care or combined music therapy/standard care. Early versus late treatment using RAS in gait training has been trialed (Hayden et al., 2009), but music therapy treatment for upper limb rehabilitation has not been investigated using a wait list design. The feasibility of delivering RAS for stroke patients as part of standard care has been explored (Hayden et al., 2009). Owing to the innovative nature of this intervention and recruitment of participants from within an NHS trust where neurologic music therapy is not recognized or available, participants will be recruited after discharge from community stroke rehabilitation services.

The study reported here will build upon the existing knowledge of music's effect on neuroplasticity (Schneider et al., 2007; Altenmüller et al., 2009; Rojo et al., 2011; Amengual et al., 2013) and translate this knowledge into a clinical protocol that may improve patient outcomes. Thus, it will add to limited, existing research into musical instrument playing, rhythm and upper limb rehabilitation following stroke. It will also address questions concerning dosage, setting and the timing of treatment delivery. Whereas most of the research to date on this topic has been laboratory based, this study provides a novel intervention that will be delivered one-to-one, in participants' homes. It will therefore examine the feasibility of home treatment delivery at the end of standard community care. In addition, participant experience of TIMP recorded via semi-structured interview will provide data regarding motivation, access and compliance to treatment. Frequency of sessions will be reduced compared to previous studies, in order to determine whether it is still effective at a lower dosage and to ensure that the sample size can be treated within the timeframes and resources available for this research.

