### Recruitment

Participants will be recruited from three geographically separate community stroke rehabilitation teams in the south of England. Patients discharged from community rehabilitation who meet the inclusion criteria will be invited by the host NHS trust to participate in this study. It will not be possible to control for the length of time that each participant receives statutory community rehabilitation prior to joining the study, as within the host NHS trust this is extremely variable. Music therapy is also not recognized as an intervention for upper limb hemiparesis following stroke in the UK. As such, the host NHS trust cannot agree to facilitate any disruption or adjustment to standard treatment for their patients for music therapy research purposes. Such bodies as the Care Quality Commission (CQC) (Care Quality Commission, 2011) and National Institute for Clinical Excellence (NICE) (National Institute For Health and Care Excellence, 2013) do not recommend music therapy as an intervention with stroke patients. However, following a review of music therapy and traumatic brain injury by the Cochrane library, music therapy is now listed as a possible intervention within neurorehabilitation (Bradt et al., 2010). Potential participants who meet the inclusion criteria and, following invitation by the host NHS trust, have expressed an interest in the study will be visited in their home by the researcher in order to demonstrate the treatment methods, including the playing patterns, and answer any questions. All participants will be required to give informed consent, which will be recorded.

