### Participants

Fourteen adult participants, 3–60 months post stroke, with hemiparesis will be recruited who have been discharged from community rehabilitation and can consent to treatment. The age range for inclusion will be 18–90. As with the MST studies (Schneider et al., 2007; Altenmüller et al., 2009; Rojo et al., 2011; Amengual et al., 2013) participants must be able to lift their affected hand up on to a table whilst seated, unaided by their unaffected side and have some finger movement in the affected hand. In a meta-analysis of literature reporting prognostic variables in upper limb recovery (Coupar et al., 2012), inconclusive evidence was found for time since stroke being a predictor. Comparisons between lesion site also revealed no predictive value in upper limb recovery. The most significant findings were that patients recovered significantly more upper limb function if there was less impairment in their upper limb initially caused by the stroke. The inclusion criteria for this feasibility study has been determined based on this research and that set for the MST studies earlier cited. On entry into the study participants will be randomized to either the treatment or wait list group, with a list of numbers randomly generated by an independent statistician using a computer, which will be concealed using opaque sealed envelopes. The assessor will be blinded to participant allocation. In order to maintain blinding the researcher will deliver a script for all participants and the assessor at each assessment time-point.

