### Statistical analysis

For the primary outcome measures, for the appropriate analysis of the crossover design with repeated measures, a linear mixed model approach will be used. This will be undertaken using the computer program R and will employ the R package lme4, which is sufficiently flexible to provide detailed analysis for this type of design, including the accommodation of missing values. The main result of this analysis will be the assessment of whether the music therapy has had an effect. To avoid the need to make strong assumptions about the distribution of the data, namely, that fitted model residuals are Normally distributed, computer-intensive methods will be employed for the statistical inferences. This will include bootstrap approaches to calculating 95% confidence limits, and permutation tests to obtain statistical significance test *P*-values.

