Thus, the intention of this feasibility study is to provide and test a platform, via the TIMP playing patterns, for breaking down movement sequences, facilitating a high level of repetition of specific movements within an activity that is interactive and enjoyable and that is clearly linked to movements required for ADLs. Exercises are performed within clearly structured and repeated rhythmic, musical frameworks, the like of which are evidenced as potential drivers of neural reorganization specifically in the realm of stroke hemiparesis rehabilitation, and also found to reduce learned misuse or compensatory motor behaviors.

Although in this feasibility study, with a small sample size, we do not predict significant group outcomes, we still expect to report on feasibility of the delivery and efficacy of the intervention. We are not intending to apply non-parametric statistical analysis and aren't expecting larger generalizability of the data (which would be increased by applying non-parametrical testing) but want to explore tendencies achievable with parametric data analysis strategies, research design and conditions that would apply with a larger and powered sample size.

MST and trials investigating the effects of rhythm and music on upper limb kinematics have taken place in research laboratories and included, predominantly, inpatients 2 months post stroke. This TIMP study includes participants up to 5 years post stroke, where community rehabilitation in their home has been completed. The majority of rehabilitation for stroke patients in the UK takes place in patients' homes and does not target upper limb hemiparesis alone, but mobility and independent living skills in a more holistic model. To date there have been no reports on feasibility for this type of intervention in participants' homes. As such the study will make a contribution to new knowledge in the field that could influence future service design.

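### The bar on outside upper-limb rehabilitation is stated only for wait-list participants before TIMP, so the rule differs by arm; the likely bias is small and its net direction unknown

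*Protocol article*

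**What the plan says.** The only rule on outside therapy is in the Procedure section: "Whilst in wait list, before the intervention begins, participants will not receive any community nor privately employed rehabilitation interventions for upper limb hemiparesis". It is limited by arm (wait list) and by time (until TIMP starts). The sentence before it says that the researcher sets no practice between sessions. That covers the researcher's own exercises, not therapy obtained elsewhere.

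The same section relies on the comparison that the rule protects: "The design will allow analysis of treatment and no treatment by comparing treatment group with wait list group data". It adds a second use of the untreated weeks: "Data collected from wait list group participants prior to TIMP treatment will be analyzed to determine whether there has been any spontaneous change". The Statistical analysis section says of the mixed model: "The main result of this analysis will be the assessment of whether the music therapy has had an effect". The Discussion predicts no significant group outcomes, but states that "we still expect to report on feasibility of the delivery and efficacy of the intervention".

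Three statements bear on how much outside therapy there could be:
- Background: "participants will be recruited after discharge from community stroke rehabilitation services".
- Participants: those recruited are people "who have been discharged from community rehabilitation and can consent to treatment".
- Recruitment: "the host NHS trust cannot agree to facilitate any disruption or adjustment to standard treatment".

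**The concern.** A restriction that starts after randomization and applies to one arm only is a difference between the arms other than TIMP. Randomization balances the arms at entry, but it cannot correct a conduct rule that differs by arm afterwards. If the rule is followed as written, a wait-list participant in Weeks 1-9 has no outside upper-limb therapy, while a treatment-arm participant in those weeks may have some. Any benefit would then be credited to TIMP.

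A second problem lies within the wait-list arm. Its bar ends when its TIMP starts, so private therapy taken up at that point would coincide with TIMP and be counted in that arm's before/after change.

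At stake is the efficacy signal that the study means to report, and the conduct rule that a larger trial might inherit.

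**Working it through.** The plan gives no figure to reproduce. The check has two parts: who is restricted when, and how far outside therapy could move the results.

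**Coverage of the rule, by calendar period** (assessments at Weeks 1, 6, 9, 15 and 18, from Procedure)

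| Weeks | Treatment arm | Wait-list arm | Effect of beneficial outside therapy in an unrestricted arm |
|---|---|---|---|
| 1-6 | TIMP, no bar stated | Waiting, barred | Raises the treated arm: toward TIMP |
| 6-9 | After TIMP, no bar stated | Waiting, barred | Raises the already treated arm: toward TIMP in the Week 9 contrast |
| 9-15 | After TIMP, no bar stated | TIMP, bar has ended | In the wait-list arm: toward TIMP (before/after). In the treatment arm, then off treatment: against TIMP |
| 15-18 | After TIMP, no bar stated | After TIMP, no bar stated | Affects follow-up in both arms |

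The direction is therefore toward TIMP in two comparisons: treatment versus wait list before Week 9, and the wait-list arm before versus after its own TIMP. In Weeks 9-15, outside therapy in the treatment arm pulls the other way. The mixed model uses all five time points, so its net direction cannot be derived from the document.

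**Size**

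Inputs: 7 per arm (Abstract). The document gives none of the following, so they are assumed: a gain g of 1 to 6 ARAT points per affected participant, k = 1 or 2 affected participants in an arm, and an SD of ARAT change of 3 to 6 points.

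Shift in an arm mean = k × g / 7:
- k = 1: 1/7 = 0.14; 3/7 = 0.43; 6/7 = 0.86
- k = 2: 2/7 = 0.29; 6/7 = 0.86; 12/7 = 1.71

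Standard error of a simple between-arm difference = SD × √(1/7 + 1/7) = 0.535 × SD:
- SD 3: 1.60
- SD 6: 3.21

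One participant gaining 3 points: 0.43/3.21 = 0.13 to 0.43/1.60 = 0.27 standard errors.

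Most extreme corner of the range (two participants gaining 6 points each, SD 3): 1.71/1.60 = 1.07 standard errors.

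For the wait-list before/after comparison, standard error = SD/√7 = 0.378 × SD:
- SD 3: 1.13
- SD 6: 2.27

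One participant gaining 3 points: 0.43/2.27 = 0.19 to 0.43/1.13 = 0.38 standard errors.

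**The case against.** **This is only silence in a condensed article.** The Procedure sentence defines the no-treatment condition and contradicts nothing. Rules on concomitant care are often left to the full protocol, which may extend the bar to everyone, and Figure 1 is not shown. This stands in part: a reader might infer that the plan allows outside therapy in the treatment arm, but no sentence permits it. Even so, the article is not silent on the subject. It states a rule and limits it to one arm and one period.

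**Eligibility already removes the main exposure.** This stands. A reader might infer that statutory community therapy continues in one arm, but everyone is discharged before entry. The host trust's refusal to adjust standard treatment helps explain why recruitment follows discharge; it does not show that re-referral is expected. What is left is private therapy or re-referral, with no rate given. The authors nevertheless thought it worth barring both community and private therapy in these discharged patients, and nothing suggests the possibility exists in one arm only.

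**The bias is not one-directional.** This stands. A reader might infer that the gap always favours TIMP. That holds only for the two comparisons named above and fails in Weeks 9-15.

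**Restricting each arm only through its own TIMP period would recreate the fault.** This also stands. Barring the treatment arm for Weeks 1-9 and the wait-list arm for Weeks 1-15 leaves one arm barred and its concurrent comparator free in Weeks 9-15. The remedy has to match in calendar time.

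**It cannot matter in a 14-person feasibility study.** This lowers the severity but does not remove the point. The study was not sized by power, but it still makes an assessment of effect the main result of its model.

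**Conclusion.** The point holds in a limited form. The bar on outside upper-limb rehabilitation, as stated, differs between arms in the weeks when they are compared, and it does not cover either arm during TIMP. The early between-arm contrast and the wait-list before/after comparison could be tilted toward TIMP. Outside therapy in the treatment arm in Weeks 9-15 could work against it, and the net effect on the full model is unknown.

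The likely size is small: about 0.1 to 0.4 standard errors for one participant gaining 3 points across the two comparisons. It approaches or exceeds one standard error only if two of seven participants in an arm gain near the top of the range and the SD is at its low end. All of this rests on assumed gains, SDs and counts, and on no extension of the rule in the full protocol.

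The document does not support a claim of large or systematic bias, or that outside therapy is known to occur. Severity is minor; the reason to act is that the remedy is cheap and the study prepares a larger trial.

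**What to change.** Reword the Procedure rule so that the same bar on community and private upper-limb rehabilitation applies to both arms over the same calendar weeks. Weeks 1-9 is the minimum and protects the early contrast. Weeks 1-15 is better, as it also covers the wait-list arm's TIMP period and keeps the arms alike during it. Extending to Week 18 would protect the last follow-up as well.

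Where the bar cannot be applied, for example after NHS re-referral or when a participant chooses private therapy, ask about and record outside upper-limb therapy in both arms at each of the five existing assessments. The contrast should then be interpreted in that light. The researcher rather than the blinded assessor should ask, so that the answers do not hint at allocation.

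Cost: no new visits or outcome measures. Participants forgo private upper-limb therapy for the stated weeks:
- To Week 9: about 9 weeks for the treatment arm, no change for the wait-list arm.
- To Week 15: about 15 weeks for the treatment arm, and about 15 − 9 = 6 more than now for the wait-list arm.
- To Week 18: about 18 weeks for the treatment arm, and about 18 − 9 = 9 more than now for the wait-list arm.

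The consent wording may need a small amendment. If the longer restriction is judged too burdensome, use the Weeks 1-9 bar with recording through Week 18.

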## Methods

### Study design

A cross-over design with repeated measures will be used, with participants being randomized into either a wait list or treatment group (see Figure 1). Assessments for each participant will take place at the same time points after baseline measure, as illustrated in Figure 1, with the baseline and end assessments immediately before and after the 6 weeks of TIMP being conducted by a therapist who is blind to participant allocation.

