**Figure 1 F1:**
[figure not shown]
**Study consort, showing the crossover design with repeated measures**. BA, Blind Assessor, who will conduct ARAT and 9HPT indicated at Weeks 1 and 6 (treatment), 9 and 15 (wait list).

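### The first ARAT/9HPT follows randomisation and is listed as blind-rated in the treatment arm only, and the week labels around the 6-week course cannot be reconciled between arms

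*Protocol article*

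**What the plan says.** All references are to the protocol article.

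- **Order of events.** Participants section: "On entry into the study participants will be randomized to either the treatment or wait list group". The allocation list is drawn by computer by a statistician outside the study team and is hidden in sealed envelopes. Procedure section, on the assessments: "Timepoint 1 at Week 1 after randomization; timepoint 2 at week 6; timepoint 3 at week 9; timepoint 4 at week 15", with timepoint 5 at week 18. No ARAT or 9HPT before randomisation is described.
- **Who rates blind.** The Participants section says in general terms "The assessor will be blinded to participant allocation", and adds "In order to maintain blinding the researcher will deliver a script for all participants and the assessor at each assessment time-point". The Study design section is narrower. It speaks of the assessments "immediately before and after the 6 weeks of TIMP being conducted by a therapist who is blind to participant allocation". The Figure 1 legend names the visits of the blind assessor, "who will conduct ARAT and 9HPT indicated at Weeks 1 and 6 (treatment), 9 and 15 (wait list".
- **Course length.** The Procedure section gives every participant 12 sessions, two a week for 6 weeks.
- **Use of the data.** The Procedure section compares the treatment group with the wait list (treatment versus no treatment) and early with late intervention. ARAT is the primary outcome (Measures), analysed with a linear mixed model (Statistical analysis).

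**The concern.** A baseline should be beyond the reach of the allocation. Here it is measured once the arm has been assigned. A wait-list design cannot hide the arm from the participant, and the researcher who delivers TIMP alone (Sample size section) must know it as well. Blind rating is then the remaining protection, and at Week 1 it is listed for one arm only. The first blind-assessor visit also falls at a different week in each arm, so the visit itself could hint at the allocation.

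What is at stake is the starting value of the primary outcome in the comparison of treatment with no treatment. The week labels are a separate matter: if the two before-after windows differ in length, the within-person changes and the early-versus-late contrast do not compare like with like, and it is unclear what elapsed time a model should use.

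**Working it through.** **1. Order.** Randomisation is on entry, and timepoint 1 is dated after randomisation. Whether Week 1 means the same day, some day in the first week, or seven days later, it comes after allocation. The Procedure section does refer to time points after a baseline measure, but the five it lists start at Week 1, and the Abstract also counts five repeated measures. In the treatment arm, timepoint 1 is the only test described before TIMP. No separate earlier baseline is described.

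**2. Visits listed for the blind assessor** (Figure 1 legend, in line with Study design).

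| Visit | Treatment arm | Wait list arm |
|---|---|---|
| Week 1 | listed | not listed |
| Week 6 | listed | not listed |
| Week 9 | not listed | listed |
| Week 15 | not listed | listed |
| Week 18 | not listed | not listed |

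The randomised comparison of treatment with no treatment uses the first two rows.

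**3. Effect of a shifted starting value.** Let D = (T2 − T1) in the treatment arm minus (T2 − T1) in the wait list. If the wait-list T1 is off by b ARAT points, D moves by +b: 1 point gives 1 point, 2 points give 2. If the baseline is instead a covariate with slope β, the adjusted difference moves by β × b. An equal shift in the wait-list Week 6 rating would cancel in D. The documents give no figure for b, so its size is unknown.

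**4. Week labels.** Stated course: 12 sessions ÷ 2 per week = 6 weeks, in both arms.

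- Labels as elapsed weeks: 6 − 1 = 5 (treatment) and 15 − 9 = 6 (wait list).
- Start of the first labelled week to the end of the last: 6 − 1 + 1 = 6 and 15 − 9 + 1 = 7.
- In general, a uniform rule adds the same constant c to both windows: 5 + c and 6 + c. They always differ by one week, so no uniform rule gives 6 and 6.
- Only a mixed reading works, with timepoint 1 as week 0 and the other labels as elapsed weeks: 6 − 0 = 6 and 15 − 9 = 6. The successive gaps are then 6, 3, 6 and 3 weeks, 18 in total.

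The stated 6 weeks in both arms is therefore not reproduced from the labels under one rule.

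**5. Which comparisons are touched.** Timepoints 1 and 2 carry the same labels in both arms, so the randomised contrast has equal length in each (5 weeks by label, 6 if timepoint 1 is week 0). The unequal windows arise only when Weeks 1 to 6 in one arm are set against Weeks 9 to 15 in the other.

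**The case against.** The best defence is that the Participants section states assessor blinding without restriction and provides a script at every assessment. That shows the intention, and it rules out saying that the assessor knows the allocation. It does not settle who rates the wait list at Week 1, because the two more specific statements leave that visit out. If their list is merely incomplete, the passages still need to be reconciled, and the test still follows allocation.

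Several stronger readings are tempting, but the documents do not support them.

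- *The baseline comes a full week after randomisation.* This is one reading of Week 1. The first week or day 0 is equally possible.
- *Only 10 of the 12 sessions fit between Weeks 1 and 6.* This takes the label literally (5 × 2). Study design puts the tests directly before and after the 6 weeks, and Procedure fixes 12 sessions for everyone. It is a labelling fault, not a shorter planned course.
- *The 9-week delay conflicts with an 8-week gap from Week 1 to Week 9.* Procedure counts that delay from community discharge to the start of TIMP, not from timepoint 1, so there is no conflict.
- *Severity should have governed the allocation.* The finding cited in the Participants section is that "patients recovered significantly more upper limb function if there was less impairment in their upper limb initially caused by the stroke". That concerns severity at onset, whereas entry is 3–60 months later and ARAT at entry is a different measurement. The chance imbalance can be computed: SD √(2/7) = 0.53 of a participant SD, with a 35% probability of exceeding 0.5 SD and 6% of exceeding 1 SD by normal approximation. It is the same for any unstratified 7 v 7 trial and is not bias in the treatment estimate. Stratifying 14 people who enter one at a time, with no cut-off defined, is a debatable trade-off.
- *Participants will leave, or try less hard, on learning their arm.* This is possible, but nothing in the document documents it.

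It is also fair that this is a feasibility study expecting no significant group result, and that covariates and time coding may sit in an analysis plan not shown. The order of testing and allocation, the rater and the visit weeks are design facts stated here, however, and the Discussion says the design is meant to reflect what a larger, powered study would use.

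**Conclusion.** The point holds in two parts.

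First, as written, the starting ARAT and 9HPT are taken after allocation in both arms, and in the wait list they are not listed as blind. This rests on the wording of Participants, Procedure, Study design and the Figure 1 legend; the figure itself is not shown. The effect on a change-score comparison is one for one with any shift in that value, and the size of such a shift is not known. A reader might infer that the baseline is useless for adjustment. It is not: a test taken before treatment starts can still enter the model, with the caveat that one arm's value may be unblinded.

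Second, the labels give windows that differ by one week under any uniform count, against a stated 6 weeks in both arms. This concerns the before-after and early-versus-late comparisons only.

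Both are worth correcting. Neither shows that results would be biased.

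**What to change.** 1. Do the timepoint 1 ARAT and 9HPT after consent and before the allocation envelope is opened, in both arms. Provided that the envelopes keep the allocation concealed as described, the rating is then blind to arm whoever does it.
2. Use that pre-allocation ARAT as the baseline in the mixed model.
3. Reconcile the week labels in the Procedure section and the Figure 1 legend with the stated 6-week course, for example by labelling timepoint 1 as week 0.
4. Align the general blinding statement in Participants with the visits listed in Study design and Figure 1.

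The cost is small. Two existing steps change order, no visit is added, and a rater must be scheduled before allocation. Because nobody knows the arm at that point, one arrangement serves all 14 participants. The change protects the starting value only. The wait-list Week 6 test is also absent from the blind list, and reordering does not cure that.
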